**Co-primary and secondary outcome measures:**

ORVAC has two co-primary outcomes: (1) anti-rotavirus IgA seroconversion, defined as serum anti-rotavirus IgA ≥ 20 U/ml 28 to 55 days post Rotarix/placebo, and (2) time from randomisation to medical attendance for which the primary reason for presentation is acute gastroenteritis or acute diarrhoea illness before age 36 months. Secondary outcomes include (1) change in anti-rotavirus IgA log titre, (2) time from randomisation to hospitalisation with primary admission code presumed or confirmed acute diarrhoea illness before age 36 months, (3) time from randomisation to hospitalisation for which the admission is rotavirus confirmed diarrhoea illness before age 36 months and (4) time from randomisation to rotavirus infection (not necessarily requiring hospitalisation) meeting the jurisdictional definition before age 36 months.

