## ORVAC study design

ORVAC is a pragmatic, investigator-led, double-blind, randomised, placebo-controlled Bayesian adaptive clinical trial testing a third scheduled dose of Rotarix rotavirus vaccine (versus usual care) in Australian Indigenous infants to improve protection against clinically important gastroenteritis. It has the following key features:
Double-blind, randomised, placebo-controlled trial (neither the outcome observer nor participant’s caregivers know the treatment status);Non-fixed sample size up to 1000 participants (up to the first 250 with venous sampling) based on Bayesian stopping rules (minimum sample size of 70 for predicting futility);Fixed 1:1 parallel group enrolment into the active and control arm throughout the trial;Frequent interim analyses;Evaluation of intervention effects in the Darwin urban region compared to remote/very remote regions; andStudy participation is from randomisation until the end of follow-up at 36 months of age.

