## Trial population

ORVAC has two population subgroups: (1) children who normally reside in a major city, an inner or outer regional area and (2) children residing in remote or very remote areas according to the Australian Government Department of Health Australian Standard Geographical Classification-Remoteness Area (ASGC-RA) system. While baseline characteristics for immunological status and median time to medical attendance/hospitalisation are not well understood for this population, comparable settings have an RV vaccine efficacy of around 50%. However, in the NT Indigenous population, protection has been noted to wane after the first year of life, estimated to fall to a rate of only 10% [22]. Estimates for the rate of hospitalisations due to acute gastroenteritis are also highly variable with median times to hospitalisations reported to be between 15 and 40 months from birth [1].

The clinical data from this trial will be analysed and reported on an intention-to-treat (ITT) basis with all randomised participants contributing to the analysis of the co-primary endpoints. Specifically, for the ITT analysis:
Patients will be analysed in the group they were allocated to;Patients not receiving Rotarix/placebo will be retained;False inclusions will be retained;Protocol deviations will not result in exclusion; andThe potential effect of missing values will be examined (see later).

We will also produce companion analyses on a per-protocol (PP) basis using the subset of participants that completed without protocol violation.

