### Co-primary

The primary objective is quantified through a clinical and an immunological outcome designed to measure the clinical effectiveness of an additional scheduled dose and any change in the immune response.

The immunological outcome is anti-rotavirus IgA seroconversion, defined as serum anti-rotavirus IgA ≥ 20 U/ml at 28 to 55 days post Rotarix/placebo among infants with anti-rotavirus serum IgA < 20 U/ml prior to administering the third dose.

The clinical outcome is the time from randomisation to first medical attendance (hospitalisation, emergency department presentation, medical clinic presentation) for which the primary reason for presentation is presumed or confirmed all-cause acute gastroenteritis or acute diarrhoea illness between randomisation and age 36 months.

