### Descriptive statistics

Participant characteristics will be summarised by treatment group and stratified by locality. No formal statistical testing will be performed to compare groups at this stage. We will provide quantitative summaries of the participant data including:
Number of participants in ITT;Age at randomisation;Number of prior doses of Rotarix vaccination;Sex;Common comorbidities at randomisation;Breast feeding status;Anthropometric indices;Location of residence (urban versus remote);Proportion seropositive at baseline and seropositive/seroconverted at follow-up;Change in anti-rotavirus IgA between administration and second follow-up;Frequency of medical attendance events;Time to medical attendance events;Frequency of censoring;Frequency of intussusception;Frequency of adverse events; andOccurrence and timing of gastroenteritis outbreaks by community.

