### Interim analyses of co-primary outcomes

Bayesian adaptive trials rely on accumulating data and pre-specified decision rules to trigger adaptations. However, in order to ensure trial integrity, extensive simulation of the trial is required to investigate and quantify the operating characteristics such as the type I error rates, power and expected sample size under a range of hypothetical trial scenarios.

In this section, we outline the decision processes used for the interim analyses. Details on the simulations that were used to evaluate the operating characteristics of the trial are provided in a later section.

A simplified flow chart for the interim analyses and decision rules is presented in Fig. 1. The first interim analysis on the immunological endpoint will occur when 70 participants have full (baseline and follow-up) immunologic results. Further interim analyses occur after every subsequent 50 children or after every 3 months, whichever occurs sooner, unless there have been no new entrants. If there are no new blood samples and/or events, then we will defer the full analysis until the next scheduled interim. Analysis of the clinical endpoint will start when 200 children are enrolled in order that there are enough events to meaningfully undertake a time-to-event analysis.

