Next, we will test for futility by computing the predictive probability of observing a treatment effect under the assumption that we continue to the maximum sample size (*n* = 250) for the immunological endpoint. A predictive probability is computed using the following steps.
Take a draw from the joint posterior distribution.Use the draw to simulate random variables from a Bernoulli distribution to impute the immunological results that are not yet available for the enrolled participants with pending immunological results and the immunological results for future participants that are currently unenrolled up to the maximum sample size of 250.Combine the observed and the simulated data to form a complete dataset.Fit a logistic regression model to the complete dataset and compute the probability that the treatment effect is above zero.If the probability that the treatment effect is greater than zero is above a threshold value, then consider the trial successful and increment a counter of the number of successful trials.Go back to step 1, repeating the process at least 1000 times.

At the end of the process, we know the number of times that the trial was deemed successful from which we can compute the probability of predicted success (PPoS) as:
6$$\begin{array}{*{20}l} \textrm{PPoS}= \frac{1}{k} \sum_{1}^{k} \mathrm{I}[\mathbb{P}(\beta_{\text{trt}}>0)>0.97] \end{array} $$

where I() represents an indicator function evaluating to 1 if the contained expression is true and 0 otherwise, *β*_trt_ is the log odds ratio of seroconversion in the treatment arm versus the control arm and *k* is the total number of simulated datasets. If the PPoS is less than the futility threshold, then stop for futility and cease enrolment.

Next, if futility was not established, repeat the above process; however, only impute for the enrolled participants that do not yet have complete immunological data. If the resultant PPoS is greater than the threshold to stop venous sampling, we will cease venous sampling. If either the futility or stop venous sampling thresholds are triggered, we will undertake a final analysis on the immunological outcome once all the enrolled participants (at the time of the trigger) have been followed to completion.

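### The immunological co-primary is defined with and without a baseline-seronegative restriction, and the model fit, futility imputation and stated power do not fit the restricted definition

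*SAP article*

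**What the plan says.** The Co-primary section counts an infant as seroconverted if IgA is at least 20 U/ml at 28 to 55 days "post Rotarix/placebo among infants with anti-rotavirus serum IgA" below 20 U/ml before the dose. The abstract gives "anti-rotavirus IgA seroconversion, defined as serum anti-rotavirus IgA" of at least 20 U/ml in the same window, with no condition on the baseline value.

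The operational sections count sampled infants:
- ORVAC study design sets the cap at "up to the first 250 with venous sampling".
- Interim analyses of co-primary outcomes places the first look "when 70 participants have full (baseline and follow-up) immunologic results". It fits the logistic model to all complete immunological results. For futility it imputes all pending results and "the immunological results for future participants that are currently unenrolled up to the maximum sample size of 250".
- Evaluation of operating characteristics simulates seroconversion as independent Bernoulli trials, with control rates of 0.1 to 0.7 and differences of 0 to 0.15. It mentions no share of infants seropositive at baseline.

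Baseline seropositives are foreseen. Rotarix is already scheduled at 2 and 4 months (Background), and Descriptive statistics will report "Proportion seropositive at baseline and seropositive/seroconverted at follow-up". No section says whether these infants are excluded, counted as failures or counted as successes.

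**The concern.** The two definitions are different estimands: conversion among infants who could convert, and seropositivity after the dose among all sampled infants. Under the restricted definition, an infant already at or above 20 U/ml has no outcome. The futility step would nevertheless generate one for every future infant up to 250, and the power statement would rest on more evaluable infants than the trial will have.

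The stakes go beyond the immunological result. Immunological futility stops enrolment into a trial of up to 1000 infants, and futility on either outcome blocks the test for expected success. The article reports that four interim analyses had been run by August 2020, so how seropositives are counted bears on a rule already in use.

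**Working it through.** **Inputs.** At most 250 infants sampled, allocated 1:1, so 125 per arm. Win threshold 0.97, taken as one-sided 0.03 with z = 1.881. Stated power (Sample size, power and expected success): control 0.4, around 40% for +0.10 and around 70% for +0.15; control 0.1, over 60% for +0.10 and well over 80% for +0.15. The baseline-seropositive share q is not in the document; 10%, 30% and 50% are assumptions.

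**Step 1: reproduce the stated power.** For n evaluable infants in total,

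Power = Φ( (p1 − p0) / √[(p0(1 − p0) + p1(1 − p1)) / (n/2)] − 1.881 ).

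For 0.4 v 0.5 and n = 250: √(0.49/125) = 0.0626; 0.10/0.0626 = 1.597; Φ(1.597 − 1.881) = 39%. The other three scenarios give 70%, 64% and 90%. A simulation with interim looks gave 40.2%, 69.4%, 62.5% and 88.5%. It used looks at 70, 120, 170 and 220 infants, thresholds 0.97, 0.05 and 0.90, beta-binomial analysis with a normal approximation, about 12 results pending (assumed) and 4000 trials. Both sets match the article, so its power corresponds to about 250 evaluable infants.

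**Step 2: apply the Co-primary restriction.** Evaluable n = 250 × (1 − q).

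| q (assumed) | n evaluable | 0.4 v 0.5 | 0.4 v 0.55 | 0.1 v 0.2 | 0.1 v 0.25 |
|---|---|---|---|---|---|
| 0 | 250 | 39% | 70% | 64% | 90% |
| 10% | 225 | 36% | 65% | 60% | 87% |
| 30% | 175 | 29% | 55% | 50% | 78% |
| 50% | 125 | 23% | 43% | 38% | 64% |

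The loss is about 3 to 4 percentage points at 10%, 10 to 15 at 30% and 16 to 27 at 50%. The simulation with interim looks, imputing to 250 as written, gave 32/57/48/76% at 30% and 27/46/39/65% at 50%.

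**Step 3: futility predictive probability after 70 sampled.** As written, 90 further infants per arm are imputed. Restricted to expected seronegatives, the number is 63 at q = 30% and 45 at q = 50%.

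| q | Converted among seronegatives, control v treatment | As written | Seronegatives only |
|---|---|---|---|
| 30% | 10/24 v 10/24 | 0.16 | 0.11 |
| 50% | 7/18 v 7/18 | 0.19 | 0.10 |
| 50% | 7/18 v 9/18 | 0.44 | 0.32 |

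In simulated trials at control 0.4, +0.10 and q = 50%, futility stops occurred in 46% as written and in 60% with restricted imputation.

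**Step 4: predictive probability for stopping venous sampling.** This step imputes pending infants only (6 per arm assumed). At q = 30% with 10/24 v 17/24 it is 0.74 as written and 0.87 restricted. At q = 50% with 7/18 v 10/18 it is 0.08 as written and below 0.001 restricted. The error can go either way.

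**Step 5: type I error.** At control 0.4 under the null, the simulation gave 0.041 to 0.048 with or without seropositives and under either imputation.

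**Step 6: if the abstract governs.** All 250 are evaluable. If baseline seropositives stay seropositive, a difference d among seronegatives becomes (1 − q)d overall. At q = 30%, an overall +0.15 needs 0.15/0.70 = +0.21 among seronegatives.

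**The case against.** A reader might infer that immunological power and predictive probabilities are simply overstated. The documents do not support that as an unconditional statement.

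- **The seropositive share is not given.** At an assumed 10% the loss is small. This limits the size of the problem; it does not remove the mismatch.
- **There are readings in which 250 is right.** Under the abstract every sampled infant is evaluable. Seropositives could also be coded as not seroconverted, with the simulated rates read as marginal over all sampled infants. The stated power then holds for those marginal differences. This stands, but the article does not say so, and neither reading matches the Co-primary section, where seroconversion is defined only among seronegatives.
- **Only one of the two predictive probabilities is consistently too high.** The futility one was too high in every case computed where seropositives are excluded. The one for stopping venous sampling can err in either direction.
- **The Trial population sentence is not a third definition.** The words "with all randomised participants contributing to the analysis of the co-primary endpoints" belong to a sentence that opens with the clinical data, and at most 250 of 1000 infants are bled. It cannot set the immunological denominator.
- **Scheduling a look by paired results is legitimate.** The trigger of 70 is compatible with the restriction, provided the article says that 70 counts sampled infants.
- **The abstract is a summary**, and seroconversion ordinarily implies a negative start. That favours the Co-primary definition, and it is exactly under that definition that the imputation and power do not fit.

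**Conclusion.** The concern holds conditionally. The co-primary is stated in two ways, and no operational step applies the restriction in the fuller definition. If that definition governs, the stated power is an upper bound reached only with no baseline seropositives, with losses ranging from about 3 points (10% seropositive) to about 27 points (50%); these shares are assumptions. The futility predictive probability is then too high, and immunological futility is declared too rarely. The predictive probability for stopping venous sampling is also miscalculated, in no fixed direction. Type I error is not materially affected. If the abstract governs, the power stands for overall post-dose seropositivity only, and infants already seropositive dilute the effect among those who can convert. Either way a definition must be corrected and the power tied to a named population.

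**What to change.** 1. Use one definition in the abstract and the Co-primary section. The Co-primary wording is the full body definition and the natural one to keep; the sponsor should confirm that it is intended.
2. Say in Trial population that the reference to all randomised participants does not set the immunological denominator, and state how baseline seropositives are handled.
3. Under the Co-primary definition, fit the immunological model to baseline-seronegative infants. In both predictive steps, impute outcomes only for infants known or predicted to be seronegative, drawing future infants' baseline status from the observed proportion.
4. State whether 70 and 250 count sampled or seronegative infants.
5. Restate immunological power over a range of evaluable numbers out of 250 sampled.
6. Record how seropositives were counted at the interim analyses already run.

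The cost is SAP wording, a small code change, rerun simulations and a less favourable power statement. No extra infants are needed if the lower power is accepted. Keeping 250 evaluable would instead need 250/(1 − q) sampled: about 278, 358 or 500 at 10%, 30% or 50%.

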### Secondary

The secondary objectives are exploratory and examine other aspects of effectiveness and immune response, see below and Table 1. Additionally, we will report on the safety and tolerability by examining the occurrence of intussusception potentially attributable to the intervention and the occurrence of serious adverse events.

**Table 1 Tab1:** Analysis methods for secondary outcomes

Endpoint	Overview
Time from randomisation to hospitalisation for which the primary coded reason for admission is presumed or confirmed acute gastroenteritis or acute diarrhoea illness between randomisation and age 36 months.	Summary of the median and inter-quartile range for each treatment arm. The analysis will follow the form of the analysis for the primary clinical endpoint. We will provide a competing risk analysis as discussed in the main text.
Time from randomisation to hospitalisation for which rotavirus confirmed diarrhoea illness occurs between randomisation and age 36 months.	Summary of the median and inter-quartile range for each treatment arm. The analysis will follow the form of the analysis for the primary clinical endpoint. We will provide a competing risk analysis as discussed in the main text.
Time from randomisation to rotavirus infection meeting the jurisdictional case definition between randomisation and age 36 months.	Summary of the median and inter-quartile range for each treatment arm. The analysis will follow the form of the analysis for the primary clinical endpoint. We will provide a competing risk analysis as discussed in the main text.
Change in anti-rotavirus IgA log titre between administration of intervention (RV1/placebo) and 28 to 55 days post dose.	We will adopt a robust linear regression analysis assuming the errors follow *t* distribution with between 3 and 7 degrees of freedom.
Frequency of intussusception fulfilling Brighton criteria within the first 28 days after administration of the third dose	Descriptive summary.
Frequency of serious adverse events between randomisation and age 36 months.	Descriptive summary.

Clinical outcomes comprise:
Time from randomisation to hospitalisation for which the primary coded reason for admission is presumed or confirmed acute gastroenteritis or acute diarrhoea illness before age 36 months;Time from randomisation to hospitalisation for which the primary reason for admission is rotavirus-confirmed diarrhoea illness before age 36 months; andTime from randomisation to rotavirus infection (not necessarily requiring hospitalisation) that meets the jurisdictional case definition (for disease notification) before age 36 months.

Immunological outcomes comprise:
Change in anti-rotavirus IgA log titre between administration of the Rotarix or placebo dose and 28 to 55 days post dose.

Safety outcomes comprise:
The occurrence of intussusception fulfilling Brighton criteria [24] within the first 28 days after administration of the Rotarix or placebo dose; andSerious adverse events as defined by [25] between randomisation and age 36 months.

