## Statistical analyses

ORVAC is a superiority trial that uses Bayesian methods for inference and decision-making. Unless otherwise noted, all parameter estimates will be reported as means or medians with 95% credible intervals.

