### Safety and adverse events

Two safety and tolerability outcomes are defined in the protocol: the occurrence of intussusception within the first 28 days after randomisation and the occurrence of serious adverse events between randomisation and 36 months. The occurrence of intussusception will be reported in terms of frequency and proportion, by treatment arm and overall. The serious adverse events as defined by [25] will be reported as frequency and proportion, stratified by treatment arm and overall. While no analysis will be performed on the safety and adverse event data, they will be included in the competing risk sensitivity analysis mentioned earlier.

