The expected sample size reduces as a function of clinical endpoint effect size but increases as a function of the immunological endpoint effect size. This is because the probability of ceasing the trial for futility remains high (in excess of 50%) when the immunological endpoint effect size is low. However, as the immunological endpoint effect size increases, so does the probability that the trial will continue to accumulate enough data to detect a clinical treatment effect. Based on the scenarios we simulated, we anticipate a minimum expected sample size of around 300 participants and up to a maximum sample size of 700. We anticipate that the expected number of blood samples will range from 150 to 200.

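### Intussusception and serious adverse events are to be reported as counts and proportions with no interval or arm difference, and the SAP's sections disagree on the 28-day start point and on which intussusception cases count

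*SAP article*

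**What the plan says.** Safety is a listed secondary outcome. The Secondary section introduces it with "Additionally, we will report on the safety and tolerability by examining the occurrence of intussusception potentially attributable to the intervention", and adds serious adverse events. The operational list in that section defines intussusception by the Brighton criteria within 28 days after the Rotarix or placebo dose is administered. Table 1 also counts from administration, and gives the method for both safety outcomes as a descriptive summary.

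The Safety and adverse events section spells this out. For intussusception: "The occurrence of intussusception will be reported in terms of frequency and proportion, by treatment arm and overall". Serious adverse events "will be reported as frequency and proportion, stratified by treatment arm and overall". It then states: "While no analysis will be performed on the safety and adverse event data, they will be included in the competing risk sensitivity analysis mentioned earlier". In this section the 28 days for intussusception are counted from randomisation.

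The Statistical analyses section sets a general rule that "all parameter estimates will be reported as means or medians with 95% credible intervals", but the same sentence opens with an exception for anything noted otherwise.

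On size, the section on sample size, power and expected success says "we anticipate a minimum expected sample size of around 300 participants and up to a maximum sample size of 700". The cap is 1000, with 1:1 allocation.

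**The concern.** The trial tests an additional vaccine dose and may stop well short of its cap. For a rare event at that size, an observed proportion says little, and the informative figure is the largest risk the data leave open. A plan that stops at frequency and proportion does not commit to showing it. The same holds for serious adverse events, where the useful quantity is the difference between arms and its uncertainty. Table 1 gives every other secondary outcome a model, so safety is the one domain without one.

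The count itself is also not fully fixed. Two start points for the 28 days, and wording that might or might not imply a causality filter, leave room for different tabulations of the same data. With an event this rare, including or excluding a single case changes the result.

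**Working it through.** The SAP gives no figure for safety precision, background intussusception risk or detectable risk, so there is no safety figure to reproduce.

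**Inputs.** 1:1 allocation (Randomisation). Expected total of 300 to 700 (Sample size, power and expected success), so 150 to 350 vaccinated. Cap of 1000 (ORVAC study design), so 500 vaccinated. This assumes that every infant allocated to vaccine is dosed.

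**Zero intussusception cases among n vaccinated infants.** The exact upper limit is 1 − 0.05^(1/n) one-sided 95%, and 1 − 0.025^(1/n) two-sided 95%.

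| Vaccinated n | One-sided 95% | Two-sided 95% |
|---|---|---|
| 150 | 1.98% (about 1 in 50) | 2.43% (1 in 41) |
| 350 | 0.85% (1 in 117) | 1.05% (1 in 95) |
| 500 | 0.60% (1 in 167) | 0.74% (1 in 136) |

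At the smallest mean sample size in Table 3 (242 in total, 121 per arm), the limits are 1 in 41 one-sided and 1 in 33 two-sided.

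**Effect of the prior at zero cases.** The upper 97.5% posterior point under a uniform prior, Beta(1, n+1), is 1 in 41 at n = 150 and 1 in 136 at n = 500. Under Jeffreys, Beta(0.5, n+0.5), it is 1 in 60 and 1 in 200. A Bayesian interval therefore needs its prior stated.

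**How often zero would occur.** The chance of no case is (1 − r)^n. The SAP gives no risk r, so these values are assumptions:

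| Assumed 28-day risk | n = 150 | n = 350 | n = 500 |
|---|---|---|---|
| 1 in 200 | 0.47 | 0.17 | 0.08 |
| 1 in 1000 | 0.86 | 0.71 | 0.61 |
| 1 in 10,000 | 0.99 | 0.97 | 0.95 |

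At n = 500, zero is more likely than not for any risk below 1 − 0.5^(1/500), about 1 in 720.

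**Serious adverse events.** The 95% half-width for the arm difference is about 1.96 × √(2p(1 − p)/n) with n per arm and a common risk p. The SAP gives no p, so a range is shown:

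| Assumed p | n = 150 | n = 350 | n = 500 |
|---|---|---|---|
| 10% | ±6.8 points | ±4.4 | ±3.7 |
| 20% | ±9.1 points | ±5.9 | ±5.0 |
| 30% | ±10.4 points | ±6.8 | ±5.7 |

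**The intussusception definition, side by side.**

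- Start of the 28 days: administration of the dose in Table 1 and in the Secondary list of outcomes; randomisation in Safety and adverse events. The two coincide only if dosing is on the day of randomisation. An infant randomised but never dosed has a window under one wording and none under the other.
- Case scope: the opening of the Secondary section speaks of cases that might be attributed to the intervention. Table 1, the list of outcomes and Safety and adverse events have no attribution condition.

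**The case against.** The strongest reply is that descriptive safety reporting is usual in a trial of this size, that the SAP makes no safety claim needing a test, and that Table 1 and the safety section agree on the method. That stands, and it keeps the point modest. It does not show that leaving out an interval is the better choice when adding one is nearly free.

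Several stronger readings are tempting, and the document does not support them:

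- *The plan breaks its own credible-interval rule.* It does not. The rule allows exceptions, and the safety section is one.
- *There is no safety analysis of any kind.* The sentence in question goes on to place safety events in the competing-risk sensitivity analysis. That analysis would not, as described, bound the risk of intussusception, but it is planned.
- *Readers and the data safety monitoring board could not see what risk was excluded.* Counts by arm let any reader compute the limit or compare serious adverse events between arms. What the board is shown on safety is not described here.
- *Undosed infants dilute the safety proportion.* The statement that "Patients not receiving Rotarix/placebo will be retained" sits in text on the clinical data and the co-primary endpoints. It does not fix the safety denominator, and a safety population is commonly left to the protocol.
- *Cases will be filtered by causality.* The mention of attribution is introductory, and no filter is specified. The wording only needs aligning.

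**Conclusion.** The point holds as a modest one about precision and definition. The SAP fixes safety reporting as frequency and proportion, with no interval and no arm difference. If no intussusception is seen, that would print as 0% while risks up to about 1 in 41 (150 vaccinated) or 1 in 136 (500 vaccinated) remain compatible with the data at two-sided 95%; the one-sided limits are 1 in 50 and 1 in 167. These limits rest only on the number vaccinated. That zero is the likely result is an inference, because it depends on a background risk the SAP does not give; the serious adverse event half-widths likewise rest on assumed risks of 10% to 30%.

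The firmest textual defect is the start of the 28-day window, which differs between sections and must be reconciled. The case-scope wording is a lesser inconsistency. Neither affects the efficacy design or its error rates.

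**What to change.** In Table 1 and in Safety and adverse events:

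1. Report for each arm the proportion of children with intussusception and the proportion with at least one serious adverse event, plus the vaccine-minus-placebo difference, all with two-sided 95% intervals. Use exact intervals, or beta-binomial intervals with a stated prior such as Jeffreys. With zero cases, print the upper limit beside the 0%.
2. Tabulate intussusception among dosed infants by product received, alongside the table by allocated group.
3. Reconcile the start of the 28 days, and the case scope, across the Secondary section, Table 1 and Safety and adverse events.
4. Attach no decision rule to these estimates.

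The cost is a few lines of text and simple computation on data already to be collected. The downside is a safety statement that looks less reassuring than 0%.
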